#### Aim 3 (effectiveness analysis)

The effectiveness of the *Mzake* intervention when offered by communities is determined by survey data and STI symptom interviews with a nurse at Waves 1–4. We will complete a CONSORT diagram showing recruitment, retention and loss to follow-up at each wave. We then examine significant factors associated with lost to follow-up. Identified attrition factors will be controlled in later analyses.

To evaluate the effectiveness of the intervention in improving HIV-related outcomes, we will use multi-level mixed-effects regression (for continuous outcomes) and logistic regression (for dichotomous variables) models [51]. These methods allow us to take into account time of implementation as well as lack of independence among repeated measurements and members of the same peer group. The hierarchical structure of the data is conceptualized as repeated outcome measures (level 1), nested within individuals (level 2) and nested within peer groups (level 3). Random individual and peer group effects will account for correlations between repeated measurements and between individuals from the same peer group. Intervention condition will be a time-varying covariate that reflects the stepped-wedge design in which individuals receive intervention at different stage of the study. Site and demographic factors (both individual level and community level) will be treated as fixed-effects covariates to account for differences. Time trend interactions for intervention and imporant factors will be tested to identify differential effects over time. Youth and adult data will be analyzed both together and separately. Model selections for the number of random effects and the variance-covariance structures for the outcome variables will be performed using likelihood ratio tests. Backward selection will be employed for the fixed effects. *Aim 3 analysis identifies effectiveness overall and by site.*

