**Methods:**

Three communities in southern Malawi begin implementation in randomly-assigned order using a stepped wedge design. Our evaluation sample size of 144 adults and 144 youth per community provides sufficient power to examine primary outcomes of condom use and HIV testing. Prior to any implementation, the first participants in all three communities are recruited and complete the Wave 1 baseline survey. Waves 2–4 surveys occur after each community completes roll-out. Each community follows the model’s three steps. During Prepare, the community develops a plan and trains peer group leaders. During Roll-Out, peer leaders offer the program. During Sustain, the community makes and carries out plans to continue and expand the program and ultimately obtain local funding. We evaluate degree of implementation success (Aim 1) using the community’s benchmark scores (e.g, # of peer groups held). We assess implementation process and factors related to success (Aim 2) using repeated interviews and observations, benchmarks from Aim 1 and fidelity assessments. We assess effectiveness of the peer group intervention when delivered by communities (Aim 3) using multi-level regression models to analyze data from repeated surveys. Finally, we use mixed methods analyses of all data to assess feasibility, acceptability and sustainability (Aim 4).

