To move forward, we needed a simple but effective implementation model that communities could easily use as they took ownership of the *Mzake* program and rolled it out. Most implementation models are developed for use by researchers and health professionals in clinical settings [20]. These were too complex and abstract for community use. The model needed to be accessible to individuals with less education and little exposure to formal research. An evidence-based model originally used to implement a hospital-based intervention in South Africa was the most appropriate because it had been used successfully in Africa with clinical staff, some of whom had relatively low education [21–24]. In consultation with [name], one of the model’s original developers, we adapted this model for community use. We simplified it by reducing the model from six to three major steps: *prepare, roll out and sustain.* We also developed *Mzake*-specific benchmarks for each step; the benchmarks guide implementation and are also used by communities to document their progress.

The purpose of this research is to test whether three rural communities in Phalombe, Malawi can successfully implement the *Mzake* intervention using our simple 3-Step Implementation Model. The specific aims are to:Prepare and support three communities as they use the 3-Step Model to implement the *Mzake* peer group intervention to reduce new HIV infections.Identify implementation patterns across sites and over time using mixed-methods analyses.Assess *Mzake* effectiveness when implemented by communities.Hypothesis: At each wave, participants who have completed the program will have significant improvement in HIV-related behavioral outcomes and sexually transmitted infections (STIs) compared to those in communities where the intervention has not yet been introduced.Evaluate whether the 3-Step Model is feasible, acceptable, effective and sustainable when used by communities to implement an evidence-based intervention.

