### Setting and sample

The study takes place in Phalombe District in southern Malawi. The district has a population of nearly 350,000 [30]. In consultation with District leaders, we identified one sub-district area as the most appropriate place to test the 3-step model. This area is the largest in the district; a third of the district’s population resides there. The leaders in that area selected three communities as sites for implementation.

The sample includes both the implementation partners described above, who share their perspectives on the implementation process (Aim 2), and community members, who participate in the intervention (Aim 1) and its effectiveness evaluation (Aim 3). District level leaders from government, the health sector and traditional leaders collaborate for implementation and are included in qualitative evaluation. Implementation partners in each of the three communities include a coordinating committee that will oversee implementation and the trained peer leaders. Eligibility criteria for implementation partners include being in the designated role and willingness to participate.

The community member participants include adults and youth (ages 13–19) who take part in the 7-session peer group intervention. The first 144 adults and 144 youth in each community participate in both the peer group intervention and the repeated effectiveness surveys. Participants also provide information for the process evaluation during periodic group session observations, focus groups and repeated individual interviews. Eligibility criteria for community participants include residing in the designated community and, for youth, being within the designated age range and having parental permission to participate if under age 18. We subsequently increased the number of youth recruited, because they are more likely to move away over time.

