#### Power analysis, Aim 2 effectiveness

We performed a power analysis for the stepped wedge effectiveness component to determine sample size. Conventional power calculation programs are not able to consider both the intra-class correlation (ICC) for the intervention clusters, and the ICC for repeated measures of individuals over time. Therefore, we performed 1000 simulations using the stepped wedge design, for both continuous outcomes (analyzed using mixed-effects regression) and binary outcome (analyzed using mixed-effects logistic regression) [31, 32]. We conservatively set cluster-level ICC to be 0.10, based on two previous community or classroom studies that found an ICC of 0.05 [33, 34]. Individual-level ICC was set to range from 0.2 to 0.4, as is typical for correlations between repeated measurements of an individual. We set retention rates at 85, 80, and 75% at waves 2 through 4, a conservative estimate given our prior study with 80% retention at 18 months. Expected effect sizes (0.10 to 0.20 for continuous outcomes; odds ratios ranging from 1.2 to 2.2 for dichotomous outcomes) were based on significant outcomes in our previous efficacy study [10, 11] or, for comprehensive HIV knowledge and sexually transmitted infection (STI) prevalence, a 2010 national survey [35]. With 80% statistical power, the sample of 432 persons (youth or adults) with retention rates of 75% at the last wave, supported a minimum detectable effect size of 0.13 for continuous outcome variables, and a minimum detectable odds ratio of size 1.36. Thus, we have sufficient power to detect all expected intervention effects for outcome variables for adults and youth separately.

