#### Implementation at 3 sites

We test the 3-Step Model in the 3 sites sequentially, with the order of introduction at each site randomly assigned during a public meeting. The same sequence of implementation steps and activities occurs at all sites.

During the *Prepare* step (2 months), community leaders are oriented to the program and form a site coordinating committee comprised of respected adults active in community affairs. The committee is oriented to the 3-Step Model and *Mzake.* They learn about the benchmarks which they use to develop a plan and evaluate progress every 6 months (Table 1). After making a community implementation plan, they recruit volunteers to become peer leaders. The volunteers are trained to deliver *Mzake,* maintain group records and complete a brief self-evaluation of fidelity. *The primary capacities built during this period are conceptual understanding of the* 3-Step Model *and Mzake; planning and coordination for the coordinating committee and peer group leadership skills for peer leaders.*

During *Roll-Out* (8 months), *Mzake* is introduced to community members at village meetings and those who are interested sign up to be in the peer groups and complete informed consent. The first 144 participants must also agree to complete the repeated effectiveness surveys. Peer leaders conduct the first round of 12 groups with adults, then reflect on their experiences with the coordinating committee and make any modifications. Because talking about sexuality with youth is a sensitive topic in Malawi, the leaders obtain experience and confidence with adult groups and then the same peer leaders offer 12 groups with youth. During both adult and youth groups, the research team rates fidelity and provides supportive coaching for each pair of leaders during at least one early session and one later session, rating fidelity and providing coaching to the leaders. After these initial peer groups are completed, the peer leaders and committee will meet to reflect on lessons learned and prepare for future implementation. The lessons learned from both rounds of groups will be shared with implementation partners and iteratively used to modify the 3-Step Model. *The primary capacities built during this period are: experience in using the* 3-Step Model *and offering Mzake, practical logistics for local implementation and completing the benchmarks self-evaluation for committee members.*

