#### Aim 3 effectiveness measures

Following the stepped wedge design [28, 42, 43], all adult and youth participants are recruited and consented at Wave 1 (baseline). The data collection procedure is the same for each wave. Each participant completes a brief Audio Computer-Assisted Self-Interviewing (ACASI) survey four times (Waves 1–4). We used ACASI in a previous study with young women with no problems. ACASI promotes privacy and higher reporting of sensitive sexual behaviors [44]. and was well-received by participants. To retain participants in the repeated surveys, we use standard retention strategies, including respectful interactions, repeated telephone contacts when necessary, refreshments and a small cash allowance for travel and associated.

We originally planned to obtain STI biomarkers (as indicators of unprotected sex) using rapid tests to assess the presence of three prevalent sexually transmitted infections (STIs; gonorrhea, chlamydia, and syphilis) at two time points. However, several recent studies found that the non-invasive rapid tests for gonorrhea and chlamydia had unacceptably low reliability and one was withdrawn from the market [45, 46]. Instead, we substituted a detailed systematic STI symptoms interview recommended by [name]. In her Kenya research, she found that interviews by a nurse were accurate in identifying who had an STI based on laboratory follow-up (personal communication, 11/23/2015). The nurse will refer anyone with current symptoms and follow-up within a week to ensure compliance. We discussed the planned protocol modification with our program officer at the National Institutes of Health and obtained approval. We then modified the protocol in clinicaltrials.gov.

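### The Aim 3 cohort is fixed at Wave 1, but its level-3 unit and its hypothesis depend on peer-group participation that begins about two years later at Site 3; enrolled people who never join have no defined place in the analysis

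*Protocol article*

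**What the plan says.** All places are in the protocol article.

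- **Enrolment.** The Abstract (Methods) states: "Prior to any implementation, the first participants in all three communities are recruited and complete the Wave 1 baseline survey". Aim 3 effectiveness measures agrees: "all adult and youth participants are recruited and consented at Wave 1 (baseline".
- **Joining a group.** Implementation at 3 sites puts sign-up in each site's own Roll-Out, where "those who are interested sign up to be in the peer groups and complete informed consent". It attaches the survey agreement of the first 144 to that same moment.
- **Who is a participant.** Setting and sample describes community participants as adults and youth "who take part in the 7-session peer group intervention".
- **Hypothesis.** The aims, at the end of Preliminary work prior to funding, predict that "participants who have completed the program will have significant improvement" compared with people in communities not yet reached.
- **Model.** Aim 3 (effectiveness analysis) sets out "repeated outcome measures (level 1), nested within individuals (level 2) and nested within peer groups (level 3", with random individual and peer-group effects. Intervention is a time-varying covariate. Attrition is handled by adjusting for factors associated with loss. The same section describes the target as effectiveness when communities offer the programme.
- **Retention.** The power analysis states: "We set retention rates at 85, 80, and 75% at waves 2 through 4".

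**The concern.** Membership of the cohort is settled before any implementation, but membership of a level-3 unit is settled later and only for people who join. Someone who moves, is lost or declines before their site's groups form has usable control-period surveys and no peer group. If the group identifier is missing, mixed-model procedures commonly omit the record by default, so those control surveys could go as well. Adjusting for attrition factors does not restore omitted records.

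The wording of the participant description and the hypothesis points the same way, towards people who took part or finished. Selecting on participation after enrolment gives up the like-for-like comparison that the Wave 1 cohort was meant to provide. Because the wait before joining is set by the randomised order, people at later sites have longer in which to be filtered out. At stake is which question Aim 3 answers: the effect of offering the programme in a community, or the effect in those who took it up.

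**Working it through.** **1. How long is the wait?** The inputs are Prepare 2 months, Roll-Out 8, supported sustaining 11, independent sustaining 30/18/8 months at Sites 1/2/3, and observation to Month 52. Counting back:

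- Site 1 start: 52 − 30 − 11 − 8 − 2 = month 1
- Site 2 start: 52 − 18 − 11 − 8 − 2 = month 13
- Site 3 start: 52 − 8 − 11 − 8 − 2 = month 23

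Site 3 starts 22 months after Site 1. Adding 2 months of Prepare, its adult groups form about 24 months after Site 1's start. Youth groups follow the adult round, so they form later still. If the sites instead ran back to back in 10-month steps, the figure would be 10 + 10 + 2 = 22 months. The absolute months fit poorly with district preparation in months 1–8, but the 22-month gap between sites is 30 − 8 and does not depend on that.

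**2. How many are lost before their groups start?** With 144 per age group per site and retention of 85/80/75% at Waves 2/3/4:

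- Site 2 (groups form after Wave 2): 144 × 0.15 = 21.6
- Site 3 (groups form after Wave 3): 144 × 0.20 = 28.8

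**3. How many control person-waves exist, per age stratum?** Expected numbers surveyed at Waves 1–3 are 144, 122.4 and 115.2.

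- Site 1: 144
- Site 2: 144 + 122.4 = 266.4
- Site 3: 144 + 122.4 + 115.2 = 381.6
- Total: 792

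**4. How many would go if people lost before roll-out were dropped?** This assumes the same retention at each site and that nobody lost returns.

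- Site 1: 0
- Site 2: 21.6 (Wave 1 only)
- Site 3: 28.8 at Wave 1 + (28.8 − 21.6) = 7.2 at Wave 2, giving 36.0
- Total: 57.6; 57.6/792 = 7.3%, all from Sites 2 and 3

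If people lost by the end of roll-out also never join, the losses are 21.6, 36.0 and 36.0 + 14.4 + 7.2 = 57.6. The total is 115.2, or 14.5% of 792, and (36.0 + 57.6)/115.2 = 81% of it is from Sites 2 and 3. In that case the share of each site's own control data lost is similar: 15.0%, 13.5% and 15.1%.

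**5. Does power suffer?** The protocol states a minimum detectable effect of 0.13. I used the generalised least squares variance for 3 sites and 4 waves, with cluster variance 0.10, individual ICC 0.2–0.4, fixed site effects, and (1.96 + 0.84) × SE, assuming two-sided 5%. Without a period term this gives 0.115–0.144, which brackets 0.13. Alpha and the simulation's model terms are not stated, so exact reproduction is not possible. At individual ICC 0.3 the value is 0.126 with all records, 0.127 after dropping the 57.6 person-waves and 0.129 after dropping the 115.2. With period effects the values are 0.218, 0.219 and 0.223. The change is negligible in both cases.

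**6. How far apart are the two effects?** This needs uptake, which the documents do not give. As an illustration, assume never-joining of 10/15/20% at Sites 1/2/3 (mean 15%) or 15/20/25% (mean 20%) among people who stay in the surveys, and an 8-point gain in joiners only. The effect in all enrolled is then 8 × 0.85 = 6.8 or 8 × 0.80 = 6.4 points. A simulation with these rates, and joining correlated 0.3 with baseline propensity, returned 8.0 points after deleting never-joiners, which is exactly the effect in joiners.

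**The case against.** The strongest reply is that nothing in the protocol excludes anyone. It states a hierarchy, describes it as conceptual, and leaves the number of random effects to likelihood ratio tests, so the peer-group effect may not survive. Groups could be listed at Wave 1, since 144 people and 12 groups make 12 per group. Eligibility rests on residence and, for youth, age and parental permission, not on attendance. Sessions attended are recorded as dose, and a CONSORT diagram is planned. This is a condensed article, and a rule for people without a group may sit in an analysis plan that is not shown.

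Most of this stands. Three stronger readings that a reader might infer are not supported:

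- **That never-joiners are deleted.** This is a possible software result, not a stated rule.
- **That the loss falls mainly on late-site control data whatever the cause.** This holds when attrition is the main reason for not joining. Under the assumed never-join rates in step 6 the late-site control share of removed records is (15×2 + 20×3)/(4×45) = 50% or (20×2 + 25×3)/(4×60) = 48%. With no attrition and equal never-joining at every site it is 5/12 = 42%.
- **That the effect is overstated by 18–25%.** The ratios 8/6.8 and 8/6.4 compare two different effects under assumed uptake. The simulation showed no bias in the joiners' effect.

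What the reply does not remove is the text itself. The level-3 unit is defined by later participation, the hypothesis concerns completers, and the timing of sign-up and consent is described in two ways. Separate consents for survey and programme could explain the last point, but the Roll-Out description ties the survey agreement to sign-up.

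**Conclusion.** The point holds as a mismatch to be repaired, not as a demonstrated bias. The cohort is defined at Wave 1, while the modelling unit and the hypothesis are defined by an event that comes about 24 months after Site 1's start at Site 3. An enrolled person who never joins has no level-3 unit as the model is described.

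On the protocol's own retention, and assuming that people lost before roll-out never join and are dropped, 7.3% of control person-waves per age stratum are affected, all at Sites 2 and 3. The figure is 14.5% if people lost by the end of roll-out are added. The issue is selection and an unclear analysis set, not power. How far the effect in joiners would differ from that in all enrolled cannot be stated, because it depends on uptake.

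**What to change.** - Define the primary Aim 3 set as everyone consented at Wave 1, counted as exposed from their own site's roll-out whether or not they join a group.
- Keep peer group as level 3 but give each never-joiner a single-person unit, or use a unit known for everyone at Wave 1, such as home village.
- Align the hypothesis in the aims, the participant description in Setting and sample, and the sign-up and consent text in Implementation at 3 sites with the Wave 1 enrolment in the Abstract and Aim 3 effectiveness measures.
- Report joiners or completers as a secondary analysis.

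The cost is wording and one cluster variable, with no new participants or data. The headline effect may be somewhat smaller, since it would include people who did not take up the programme. If village is used, it is a coarser grouping than peer group.

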## Methods

### Design

This study uses a hybrid design, which was developed to advance implementation science by examining both implementation processes and effectiveness in a single study [25, 26]. We give equal attention to both processes and effectiveness evaluation, a balanced design recommended where there is already evidence supporting efficacy [25].

We use a stepped wedge design to evaluate effectiveness, with staggered introduction of the intervention in three communities in randomly assigned order (Fig. 1). The stepped wedge design [27–29] has the advantage that all groups receive the intervention, which is ethically important, especially in a community intervention. This design is efficient because the repeated measures allow participants to serve as controls until the intervention is introduced in their community. In each community, the first 144 adults and 144 youth are asked to both receive the intervention and to participate in the effectiveness evaluation. Outcome measures are assessed at baseline and after each community rolls out the intervention.

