### Analysis

#### Data management and iterative analysis

Throughout the study, analysis is continuous and iterative, integrating new data as they become available. Data management protocols promote proper and timely preparation of data for analysis and secure data storage. All data are identified by location and date. A unique individual code is assigned to Individual-level data, including effectiveness evaluation data and individual interviews. Master lists linking names and code numbers will be securely stored separately from the data. Only de-identified data will be transferred from Malawi to UIC using a secure transfer system. *Quantitative data* collected include the benchmarks, Effectiveness Evaluation surveys and STI tests. The ACASI survey data are automatically entered into a database. All other data are entered by data clerks with 100% verification and transferred to data analysis programs (SAS, SPSS). *Qualitative data* (hand-written study notes and audio-recorded focus groups and individual interviews) are processed following Huberman and Miles’ recommended strategies to code, store, and retrieve data [47]. Recorded interviews and hand written notes are typed from notes or transcribed verbatim, referring to the original recordings to verify accuracy of the typed transcripts. Materials in Chichewa are translated using the same translation process described above in Measures. Transcripts and notes are imported into a qualitative data management and coding program that accepts quantitative as well as narrative data.

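### With three communities, community-level covariates add nothing beyond site, and site should be exempt from the backward selection applied to the Aim 3 fixed effects

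*Protocol article*

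**What the plan says.** The Design section describes a stepped wedge "with staggered introduction of the intervention in three communities in randomly assigned order", with measurement at four waves: "Outcome measures are assessed at baseline and after each community rolls out the intervention".

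The section Aim 3 (effectiveness analysis) sets out the model:

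- Intervention: "Intervention condition will be a time-varying covariate that reflects the stepped-wedge design in which individuals receive intervention at different stage of the study".
- Covariates: "Site and demographic factors (both individual level and community level) will be treated as fixed-effects covariates to account for differences".
- Random effects: "Random individual and peer group effects will account for correlations between repeated measurements and between individuals from the same peer group". There is no random effect for site.
- Selection: "Backward selection will be employed for the fixed effects". No term is named as protected.
- Reporting: "Aim 3 analysis identifies effectiveness overall and by site".

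No community-level factor is named. The demographic examples in Table 1 (age, education, partner status) are all individual-level.

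**The concern.** Two statements in the Aim 3 section fit badly with a three-community design.

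The first is the covariate list. Site and community-level factors are both meant to absorb differences between communities, but site alone absorbs all of them. A time-constant community factor entered beside it has no information left to use.

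The second is the selection rule. In this model the fixed site terms are the only full protection against stable differences between communities; the peer-group random effect absorbs them only in part. Site is also the randomised unit, and exposure time differs systematically between sites. Entering factors that share the site column space reduces the partial degrees of freedom on which site is judged, and the selection rule as written allows site to be removed. If it goes, part of the comparison is made between communities instead of within them. Stable community differences can then appear as an intervention effect, with a standard error that does not reflect them.

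**Working it through.** The protocol states no figure on this point, so there is none to reproduce.

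**Inputs from the protocol article.** 3 sites and 4 waves (Design); 144 adults in 12 first-round groups per site (Implementation at 3 sites), so 144/12 = 12 per group and 3 × 144 = 432 persons per stratum; individual-level ICC 0.2–0.4, cluster-level ICC 0.10, and minimum detectable effect 0.13 for continuous outcomes (Power analysis). **Assumed:** complete data, the removal threshold, and the split of variance between site and peer group.

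**1. Aliasing.** Let S2 and S3 be the indicators for sites 2 and 3, and let a community factor take values c1, c2, c3. Then

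c = c1 + (c2 − c1)·S2 + (c3 − c1)·S3,

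exactly. With values 1, 2, 4 this is c = 1 + 1·S2 + 3·S3.

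The base matrix has an intercept, 2 site, 3 wave and 1 intervention column: 1 + 2 + 3 + 1 = 7.

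| Fixed effects | Columns | Rank |
|---|---|---|
| Site, no community factor | 7 | 7 |
| Site + 1 constant community factor | 8 | 7 |
| Site + 2 | 9 | 7 |
| Site + 3 | 10 | 7 |
| 2 constant factors in place of site | 7 | 7 |
| 1 constant factor in place of site | 6 | 6 |

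A constant community factor has 0 df given site. Site has 1 df given one such factor and 0 df given two.

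**2. Effect on the intervention estimate.** In test data the intervention coefficient was −0.3357 with site alone, −0.3357 with redundant community columns added, and −0.3357 with two community factors replacing site. It moved to −0.3561 with one factor replacing site and to −0.5614 with neither. What matters is whether both between-site degrees of freedom stay fitted, not which columns carry them.

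**3. Why removing site matters.** Wave 1 precedes all roll-out and one site crosses over before each later wave, so the sites are exposed for 3, 2 and 1 of 4 waves. For illustration, take site differences of −0.2, 0 and +0.2 SD in every order, ICC 0.10 placed at peer-group level, individual ICC 0.2–0.4 and generalised least squares with wave effects. The largest bias in the intervention effect is:

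- site kept: 0;
- site dropped, nothing in its place: ±0.033 to ±0.050 SD, which is 0.033/0.13 = 25% to 0.050/0.13 = 38% of the stated detectable effect;
- one factor (values 1, 2, 4) in its place: up to about 0.010 SD, or 0.010/0.13 = 8%.

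**4. Type I error under the selection rule.** Simulation of one stratum: 432 persons, 36 groups, individual variance 0.3, site variance 0.05–0.10, peer-group variance 0–0.10, no true intervention effect, and site removed only when its own test gave p>0.05.

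- Site always kept: about 5%.
- Site subject to removal: about 5.4–6.1% overall, and 6.5–11% among runs in which it was removed. The top of the second range needs peer-group variance near zero.
- One community factor (values 1, 2, 4) left in place of site: essentially no inflation.

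The overall figure stays low because site tends to be removed when the observed site differences are small, which is when omitting it does least harm.

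**The case against.** The strongest reply is that redundancy alone is harmless. Setting aside an aliased column, whichever one it is, leaves the fitted space unchanged. A reader might infer that the fit is undefined, or that software could silently lose the site adjustment. The documents and the check do not support either inference. Only the split between site and community coefficients is undefined, and no aim depends on that split. In the check, one mixed-model routine stopped with a singular-matrix error, which is a visible failure and not a silent one. This reply stands: the adjustment can be lost only through backward selection, which could remove site even with no community factor present.

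A reader might also infer a serious error rate. If one community factor always replaced site, type I error would average about 6–27% under the same variance ranges. That is not the stated procedure, because backward selection looks at the data before removing a term.

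The aliasing also depends on reading community-level factors as measured once for each of the three communities. That is the natural reading, but the article does not say so. A village-level measure, or one that changes by wave, would not be aliased. Nothing in the article puts wave-varying health-service counts into this model, so no criticism is made on that ground.

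Finally, a condensed article may leave covariate lists and protected terms to a fuller plan, and reporting by site implies that site stays in at least some models. That limits the weight of the point but does not remove it. The article does state the joint specification and does apply selection to the fixed effects without exception, and the promise of by-site results does not protect site in the overall model.

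**Conclusion.** The point holds in a limited form. As written, the covariate specification is redundant for any time-constant factor measured at the level of the three communities: such factors have 0 df given site. The intervention effect stays estimable and unchanged while site, or factors spanning it, remain in the model. The real exposure is that the selection rule may remove site, the randomised unit, from a model with no random site term.

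The size is modest: about 5.4–6.1% type I error overall against a nominal 5%, and 6.5–11% in analyses where site is dropped. These figures rest on a p>0.05 removal rule, site variance 0.05–0.10, peer-group variance 0–0.10, individual ICC 0.3, complete data and a continuous outcome. None of them was computed for the binary primary outcomes. This is an inexpensive improvement to the analysis text and does not undermine the planned analysis.

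**What to change.** In the Aim 3 (effectiveness analysis) section:

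1. State that site is a fixed effect in every Aim 3 model (adults, youth and combined) and is exempt from backward selection.
2. Remove time-constant community-level factors from the covariate list, and adjust for individual-level demographics measured at Wave 1.
3. Use community characteristics descriptively in the Aim 4 comparison of the three cases, where differences between communities are the subject.

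The cost is a change of one or two sentences. With site forced in and the community factors removed, the matrix has 7 columns and rank 7, and the intervention estimate is the same as in the redundant model. Nothing estimable is given up, and the residual inflation from dropping site disappears.
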